#### General considerations for data analysis

Descriptive statistics will be gathered in order to determine if variables have a normal distribution and variables that violate assumptions of normality will be transformed. If this does not improve the normality of distribution, distribution free statistics will be used.

The study has pre-, mid-, post-treatment, three follow-up assessments and annual follow-up thereafter. This creates clustered data due to repeated measures. To examine treatment difference, generalized estimating equations (GEE) and a linear mixed-effects model approach (LMM) will be employed. Both approaches accommodate missing data. LMM will be the main analytical tool, particularly for estimating between-participant variability; GEE will be used to assess the robustness of the population parameters, such as treatment effects.

Analyses correlating the change in PTSD symptoms with each of the distress-related cognition and emotion variables at post-treatment will be performed, by pooling data across treatment conditions. Product-moment and Spearman’s rho correlation coefficients will be used.

Correlation analyses correlating the change in PTSD symptoms with each of the distress- related cognition and emotion variables at post-treatment, by pooling data across treatment conditions, will be performed. Product-moment and Spearman’s rho correlation coefficients will be used.

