## Objectives

### Research hypothesis

PE-A will be superior to SC as administered by counsellors in reducing PTSD symptoms at post-treatment as measured by the Child PTSD Symptom Scale – Interview (CPSS-I).PE-A treatment gains will be maintained at 3-, 6-, and 12-month follow-up and annually thereafter as measured by the CPSS-I

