### Secondary hypothesis

At post treatment PE-A will be superior to SC in reducing depression, anger, anxiety, general psychopathology, and global functioning.PE-A treatment gains will be maintained at 3-, 6-, and 12-month follow-up and annually thereafter on measures of depression, anger, anxiety, general psychopathology and global functioning.irrespective of treatment assignment (PE-A or SC), reduction in PTSD symptoms at post-treatment will be significantly and positively correlated with reduction in distress-related cognitions and emotions

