**Fig. 1 Fig1:**
[figure not shown]
Study Consort Diagram, Consort diagram

A single-blind permuted block randomized control design will be used. The proposed research aims to examine the effectiveness of a psychotherapeutic intervention administered by counsellors to treat the symptoms of PTSD in adolescents exposed to trauma. The aim is to conduct a randomized controlled trial (RCT) to compare PE-A to SC to determine the comparative effectiveness in reducing PTSD and associated symptoms in adolescents.

The study will compare the efficacy of PE-A to SC. Participation will be voluntary. All participants, who meet full PTSD or sub-threshold PTSD criteria, will be scheduled for a pre-treatment assessment with Independent Evaluators (IE). The one IE will be an experienced diagnostician and clinical psychologist and the other an experienced psychiatric nurse. Adolescents will be randomly assigned on a 1:1 ratio to receive either PE-A or SC.

Treatment will consist of 7–14 sessions of either PE or SC. The number of sessions each participant receives will be based on the weekly self-report measure of PTSD symptoms (Child PTSD Symptom Scale – Self Report; CPSS-SR); however, this will range between a minimum of 7 sessions to a maximum of 14 sessions. A 70% symptom reduction is chosen as sufficient for treatment termination.

After session five, all participants will receive a mid-treatment evaluation by the IE. The IE will again assess the participants upon termination of treatment. Participants will then enter the non-treatment follow-up phase. Participants who prematurely terminate therapy (before 70% symptom reduction or 7 sessions) will undergo a post-last session assessment with the IE and will then enter the follow-up phase. Follow-up assessments will be conducted at 3-, 6-, and 12 months post-treatment and annually thereafter. The IE assessments will comprise both structured clinical interviews and self-report measures. The assessments will cover PTSD severity, related psychopathology, general psychopathology, and PTSD-related cognitions. At the 12-month follow-up, participants who receive SC and are deemed to still have clinically significant PTSD symptoms (as determined by the IE at 12-month follow-up assessment), will be offered PE-A. To add to the rigor of the study and demonstrate the long-term efficacy of the intervention, there will be annual posttreatment follow ups, dependent on the availability of funds for this purpose.

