#### Cognition and emotion measures

Three measures of dysfunctional cognitions related to trauma will be administered to investigate the role of cognition in mechanisms of change:

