### Sample size

It is believed that the within-group effects for both PE-A and SC in this study will be comparable to the effect sizes in previous studies examining these treatments in children and adolescents and adults [26, 36, 68, 69]. Using these data, it, is suggested that a total of 64 completers is necessary to provide 80% power for a two-tailed alpha level of 0.1. The literature suggests that as many as 30% of PTSD study entrants will terminate prematurely, i.e., drop out. A total of 90 entrants will thus result in 64 completers.

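### The correlation of PTSD change with cognition and emotion change is pooled across arms without an arm term, so it can mix a between-arm difference into the association it is meant to test

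*Protocol article*

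**What the plan says.** The Secondary hypothesis section of the Protocol article states that "irrespective of treatment assignment (PE-A or SC), reduction in PTSD symptoms at post-treatment will be significantly and positively correlated with reduction" in distress-related cognitions and emotions. Secondary objectives likewise asks for the relation between change in PTSD symptoms and change in affect regulation, trauma-related cognitions and self-attributions. The section on cognition and emotion measures says that its measures of dysfunctional trauma-related cognition are given "to investigate the role of cognition in mechanisms of change".

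General considerations for data analysis specifies the test, in two nearly identical paragraphs: PTSD change is correlated "with each of the distress-related cognition and emotion variables at post-treatment will be performed, by pooling data across treatment conditions". The statistic is fixed too: "Product-moment and Spearman’s rho correlation coefficients will be used". No partial correlation, within-arm correlation or arm interaction is mentioned.

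Two other sections might have supplied an arm adjustment, but do not. The control variables under Preliminary data analysis are chosen from baseline differences for use in comparing treatments. The structural equation models under Exploratory analyses are for treatment satisfaction, compliance and guardian time, and the cognition and emotion measures are not among them.

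**The concern.** A correlation computed over both arms together has two sources: the association between the two changes within each arm, and the difference between arm means. When the arms differ on both variables in the same direction, the second source alone gives a positive coefficient. The trial expects such a difference on one of the two variables: "PE-A will be superior to SC as administered by counsellors in reducing PTSD symptoms at post-treatment".

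At stake is how a significant pooled correlation is read. It would be taken as evidence that adolescents whose cognitions improve are those whose PTSD improves, in either treatment. It could partly reflect only that one treatment did better on both measures.

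A second, smaller matter is the phrase about post-treatment in the analysis sentence. It leaves open whether the cognition and emotion variables enter as changes or as levels at that visit. The hypothesis and objective both specify change.

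**Working it through.** **Inputs from the Protocol article.** Allocation is equal: "Adolescents will be randomly assigned on a 1:1 ratio to receive either PE-A or SC" (Design). The sample size section gives "a total of 64 completers is necessary to provide 80% power for a two-tailed alpha level of 0.1", with 90 entrants and 30% dropout.

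**The plan's own figure.** 64 / 0.70 = 91.4, so 92 entrants against the stated 90; in reverse, 90 × 0.70 = 63 against 64. These agree within two participants. The article gives no figure for the correlation analysis and no effect size.

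**Arm differences (assumed).** Let d be the PE-A minus SC difference in a change score, in within-arm standard deviations. As a guide to scale, the d detectable with 32 completers per arm and 80% power is (z for alpha + 0.842) × √(2/32):
- two-sided alpha 0.10: (1.645 + 0.842) × 0.25 = 0.62
- two-sided alpha 0.05: (1.960 + 0.842) × 0.25 = 0.70

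These are back-solved, not stated in the article. The range 0.63 to 1.0 is used below.

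**Pooled correlation.** With half the sample in each arm and within-arm correlation r_w,

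r_pooled = (r_w + 0.25·d1·d2) / √[(1 + 0.25·d1²)(1 + 0.25·d2²)].

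For r_w = 0 and d1 = d2 = d this becomes 0.25d² / (1 + 0.25d²):
- d = 0.63: 0.0992 / 1.0992 = 0.09
- d = 0.70: 0.1225 / 1.1225 = 0.11
- d = 0.80: 0.16 / 1.16 = 0.14
- d = 1.0: 0.25 / 1.25 = 0.20

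**Rejection rate when the within-arm correlation is zero** (20,000 simulated trials per setting, 64 completers, two-sided nominal 5%, Pearson):

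| d on both changes | pooled, no arm term |
|---|---|
| 0.63 | 11.2% |
| 0.70 | 14.0% |
| 0.80 | 19.1% |
| 1.0 | 36.5% |

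A hand check by Fisher's z, with standard error 1/√61 = 0.128:
- d = 0.63: 0.0905 / 0.128 = 0.71, and the two tails beyond ±1.96 sum to about 11%
- d = 1.0: 0.2027 / 0.128 = 1.58, giving about 35%

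Spearman behaves the same way (13.9% at d = 0.70). More participants do not help: with 90 and d = 0.70 the Pearson rate is 17.7%.

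**When only one change differs by arm.** With d1 = 0.62 and d2 = 0 the product term vanishes, r_pooled = 0, and the simulated rate is 5.0%.

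**With arm removed** (arm-centred correlation, 61 rather than 62 degrees of freedom). The rate is 5.0% at d = 0.70 and 5.1% at d = 1.0.

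**Levels or changes.** The hypothesis predicts a positive correlation between two reductions. If post-treatment levels were used, a scale of negative cognitions such as the C-PTAS would be expected to correlate negatively with PTSD reduction, since more improvement goes with a lower score. On the NMR a higher score is better, so its sign would be opposite. The levels reading therefore fits the stated hypothesis poorly, but the sentence does not exclude it.

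**The case against.** The strongest reply is that the authors meant one overall correlation regardless of arm. Pooling estimates exactly that, and a coefficient raised because treatment moves both variables is then a real feature of the sample. This reading is available. It explains the pooling, and it means that the error rates above apply only to the claim of an association within arms. It does not let a pooled coefficient show that the association holds in either treatment, which is what the mechanism purpose needs.

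The second reply is that half of the condition is absent from the article. PE-A superiority is hypothesised for PTSD and for depression, anger, anxiety, general psychopathology and global functioning, but not for trauma cognitions, attributions or affect regulation. This stands, and the point is conditional for that reason.

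Third, the phrase about post-treatment also appears in the hypothesis, where it plainly goes with a reduction. The analysis sentence may simply mean changes measured at that visit. This stands as well: the wording is ambiguous and not shown to be wrong.

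Finally, such detail is often left to an analysis plan. That would excuse silence, but here the article names the statistic and the pooling, twice.

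**Conclusion.** The point holds in conditional form. If PE-A is better than SC on both changes, the pooled correlation overstates the within-arm association. For d between 0.63 and 1.0 on both, and no within-arm association, the spurious correlation is 0.09 to 0.20. The false-positive rate for a within-arm association is then about 11% to 37% at nominal 5% with 64 completers. The effect sizes are assumptions, the PE-A advantage on cognitions is not in the document, and without it there is no bias. The 5% level is also assumed: alpha 0.1 appears only in the sample size section, and nothing applies it to these correlations.

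A reader might infer that a successful trial would confirm the mechanism by construction, or that the objective would go unanswered. The figures do not support either. Even at d = 1.0 on both changes, some 63% of such trials would not reach significance, and near the back-solved design effect the spurious correlation is only about 0.1. Nor does the document establish that post-treatment levels will be used. The matter concerns a secondary objective and leaves the primary comparison untouched, but the remedy is nearly free.

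**What to change.** In General considerations for data analysis, replace the two duplicate paragraphs with one statement. Change from pre- to post-treatment in PTSD symptoms is correlated with change over the same interval in each cognition and emotion measure, using a partial correlation (Pearson and rank) adjusted for treatment arm, or an equivalent regression with arm as a covariate. Report each arm's own correlation beside the adjusted one. Say which direction counts as improvement on each scale, so that the predicted positive sign is unambiguous for the NMR. Adjusting for baseline values as well is optional and not needed to remove the arm effect.

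The cost is one line of text and one degree of freedom per correlation. No new data are needed.

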### Exploratory analyses

Moderators such as (pre-treatment psychopathology, education, resilience, self-esteem, perceived social support, type of trauma (sexual assault vs. physical assault), treatment expectancy and mediators (treatment satisfaction, treatment compliance, and amount of time spent with guardians in treatment sessions) will be explored to determine if they are related to treatment outcome.

In each analysis a time-by-treatment-by-moderator interaction for each of the moderators will be investigated. For each mediator, structural equations models (SEM) to model the mediated relationship to treatment conditions and each primary outcome of interest will be performed. With three assessment points at pre-, mid- and post-treatment, there is only one direct and one indirect effect of treatment condition on the response at post-treatment [67–69].

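### The test that PTSD change and cognition change are correlated pools both arms with no term for arm, so an advantage of PE-A on both variables would inflate the coefficient

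*Protocol article*

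**What the plan says.** All places are in the protocol article.

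- **Secondary hypothesis**, third item: "irrespective of treatment assignment (PE-A or SC), reduction in PTSD symptoms at post-treatment will be significantly and positively correlated with reduction in distress-related cognitions" and emotions.
- **General considerations for data analysis** fixes the test. Correlations of PTSD change with each of the cognition and emotion "variables at post-treatment will be performed, by pooling data across treatment conditions". The same plan appears in two almost identical paragraphs. On the statistic: "Product-moment and Spearman’s rho correlation coefficients will be used". Neither paragraph names an adjustment for arm, a coefficient within each arm, or an interaction with arm.
- **Research hypothesis** expects an arm effect on one of the two variables: "PE-A will be superior to SC as administered by counsellors in reducing PTSD symptoms at post-treatment".
- **Cognition and emotion measures** says that three measures of dysfunctional cognition "will be administered to investigate the role of cognition in mechanisms of change". The superiority hypothesis for secondary outcomes covers depression, anger, anxiety, general psychopathology and global functioning. It does not list cognitions or affect regulation.
- **Exploratory analyses** plans structural equation models for "mediators (treatment satisfaction, treatment compliance, and amount of time spent with guardians in treatment sessions" only. Cognitions and emotions are not among these mediators.
- **Preliminary data analysis** identifies control variables for the treatment comparison, not for this correlation.

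**The concern.** The hypothesis concerns an association between participants: do those whose PTSD improves more also improve more in cognitions and emotions? A coefficient pooled over two randomised arms measures this association plus a second component. If one arm improves more on both variables, its participants lie higher on both axes, and the gap between the arm means adds positive covariance. The pooled coefficient then partly restates the treatment effect.

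The third secondary hypothesis could therefore gain support from PE-A outperforming SC on both scales, with a weak or absent association inside each arm. The distortion grows with PE-A's advantage. It does not touch the primary outcome or any treatment comparison.

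**Working it through.** **Inputs from the article.** Allocation: "Adolescents will be randomly assigned on a 1:1 ratio to receive either PE-A or SC" (Design). Sample size gives 64 completers from 90 entrants, 30% dropout, 80% power and two-tailed alpha 0.1. It gives no effect size, and no figure is stated for the correlation analysis.

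**The plan's own figure.** 90 × 0.7 = 63, against 64 stated; 64 / 0.7 = 91.4, so 92 against 90. The entrant figure is reproduced to within two participants. The 64 itself cannot be rebuilt without an effect size. Working backwards with 32 per arm:

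d = (1.645 + 0.842) × √(2/32) = 2.487 × 0.25 = 0.62 (normal), or 0.63 with the t distribution.

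This is the only anchor for an arm difference that the article offers, and it relates to the primary comparison. Applying it to a cognition scale is my assumption.

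**Formula.** With 1:1 arms, within-arm correlation ρ, and arm differences d1 (PTSD change) and d2 (cognition variable) in within-arm SD units:

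pooled r = (ρ + d1·d2/4) / √[(1 + d1²/4)(1 + d2²/4)]

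**With ρ = 0:**

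- d1 = d2 = 0.63: 0.0992 / 1.0992 = 0.09
- d1 = d2 = 0.8: 0.16 / 1.16 = 0.14
- d1 = d2 = 1.0: 0.25 / 1.25 = 0.20
- d1 = 0.63, d2 = 0.3: 0.0473 / √(1.0992 × 1.0225) = 0.0473 / 1.060 = 0.04
- d1 = 0.63, d2 = 0: 0

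With ρ = 0.3 and d1 = d2 = 0.63, the pooled value is (0.3 + 0.0992) / 1.0992 = 0.36.

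**Rejection in the positive tail**, by simulation (Pearson, ρ = 0, at least 20,000 trials per setting). Each range runs from N = 64 to N = 90:

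| d1, d2 | two-tailed 0.1 (nominal 5%) | two-tailed 0.05 (nominal 2.5%) |
|---|---|---|
| 0.63, 0 | 5% | 2.5% |
| 0.63, 0.3 | 10-11% | 5-6% |
| 0.63, 0.63 | 17-22% | 10-13% |
| 0.8, 0.8 | 29-37% | 19-25% |
| 1.0, 1.0 | 49-62% | 36-49% |

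With arm partialled out (N − 3 degrees of freedom), rejection returns to about 5% and 2.5% in every row.

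**Does arm adjustment settle whether the relation holds in both arms?** I set the true correlation at 0.5 in PE-A and 0 in SC, at two-tailed 0.1. The arm-adjusted coefficient is significantly positive in 63-64% of trials at N = 64 and 76-77% at N = 90, whatever the arm difference. With no arm difference the pooled coefficient gives almost the same: 64% and 77%. Any single coefficient that averages over arms behaves this way.

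**Precision within an arm.** With 32 participants the Fisher z half-width is 1.96 / √29 = 0.364. An observed correlation of 0.3 then has a 95% interval from about −0.05 to 0.59.

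**The case against.** **The second arm effect is not hypothesised.** The inflation needs a shift in both variables, and the article states superiority only for PTSD symptoms and a list that leaves out cognitions and affect regulation. This stands. Calling the cognition scales mechanisms of change makes a shift plausible, no more. If only PTSD symptoms shift, pooling does no harm.

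**The size is modest.** At the one anchored value the spurious correlation is about 0.09, and the comparator is an active treatment. Differences of 1.0 have no source in the article. No alpha is stated for these correlations; 0.1 appears only under Sample size. This also stands, which is why both levels and a range of differences are shown.

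**'Irrespective of assignment' may simply mean all participants together.** On that reading hypothesis and analysis agree, and pooling is deliberate. That is a fair reading, but it does not remove the inflation: the coefficient would still combine the arm effect with the association between participants.

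**A stronger inference is tempting.** A reader might conclude that pooling is what lets a relation present only in PE-A pass as one that holds in both arms. The documents do not support this. No passage says the result will be declared for each arm, and the arm-adjusted coefficient passes such a relation nearly as often when the arms do not differ. That weakness belongs to any averaged coefficient.

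**Two coefficient types are listed.** This is not a fault here. The same section transforms non-normal variables first and then turns to distribution-free statistics, which indicates when each would apply. Both types are pooled and share the problem.

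**Conclusion.** The point holds as a modest, conditional weakness in the test of the third secondary hypothesis. The pooling is stated outright, twice, and no other part of the article adjusts this analysis for arm, so it is not a detail left to an unseen analysis plan.

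At an arm difference of 0.63 on both variables, positive-tail rejection is roughly three to four times nominal at two-tailed 0.1, and four to five times at two-tailed 0.05. It is about double at 0.63 and 0.3, and large only from about 1.0 on both. These figures assume equal arms, a within-arm correlation of exactly 0, and arm differences that the article does not give.

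A reader might also infer that a significant pooled coefficient would be wholly an artefact. That goes too far. Improvement common to both arms does not create the correlation, and where a real within-arm association exists the arm effect only adds to it (0.30 becomes 0.36 at 0.63).

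**What to change.** In General considerations for data analysis, replace the two duplicate paragraphs by one that does the following:

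1. Tests the association with an arm-adjusted coefficient: a partial correlation given arm (Pearson or rank-based), or a regression of the cognition or emotion variable on PTSD change with arm in the model.
2. Reports the coefficient with a confidence interval within each arm, and the arm-by-PTSD-change interaction.
3. Bases any statement that the relation holds in both arms on the within-arm estimates, not on the pooled or the arm-adjusted coefficient.

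The cost is a change of wording, one degree of freedom for the adjusted coefficient and one more for the interaction model. No new data are needed. The reported correlation may be smaller. With about 32 completers per arm, the within-arm and interaction estimates will be imprecise, so a non-significant interaction should not be read as evidence that the arms agree.

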### Exploratory analyses

Moderators such as (pre-treatment psychopathology, education, resilience, self-esteem, perceived social support, type of trauma (sexual assault vs. physical assault), treatment expectancy and mediators (treatment satisfaction, treatment compliance, and amount of time spent with guardians in treatment sessions) will be explored to determine if they are related to treatment outcome.

In each analysis a time-by-treatment-by-moderator interaction for each of the moderators will be investigated. For each mediator, structural equations models (SEM) to model the mediated relationship to treatment conditions and each primary outcome of interest will be performed. With three assessment points at pre-, mid- and post-treatment, there is only one direct and one indirect effect of treatment condition on the response at post-treatment [67–69].

